#### Qualitative Analysis

For RQ 4, the final reflections will be analyzed and categorized with inductive content analysis to explore the different reported effects that the course had. In addition, the participants’ goals will be analyzed at the beginning and the end of the course, examining how the goals were achieved and what factors influenced changes in behavior. These will also be used to analyze the benefits of each module on different participants. These data will be combined to get a deeper understanding of the effects of the course and the changes in the participants’ behavior.

Interview data will be analyzed using reflexive thematic analysis following Braun and Clarke [46]. The qualitative data will also be analyzed using reflexive thematic analysis following Braun and Clarke [38,46]. The analysis will adopt a primarily data-driven (inductive) approach, whereby patterns and shared meanings are identified from participants’ accounts rather than imposed a priori.

The analytic process will proceed in several phases. First, the researcher will engage in repeated reading of the interview transcripts to achieve familiarity with the data, while documenting preliminary observations and analytic reflections. Second, systematic coding will be conducted across the entire dataset. Segments of text relevant to the research questions will be identified and color-coded, with codes representing meaningful units of data that capture aspects pertinent to participants’ experiences of burnout and psychological flexibility processes. Following initial coding, codes from all interviews will be collated and examined comparatively. Through iterative review and refinement, potential themes will be developed to represent shared patterns of meaning across participants. Theme development will focus on conceptual coherence with the theoretical framework of psychological flexibility and relevance to the research questions rather than frequency alone, consistent with Braun and Clarke’s [38] guidelines. Themes will be reviewed, defined, and refined to ensure internal consistency and clear distinction between themes, resulting in a structured thematic representation of participants’ lived experiences.

### Ethical Considerations

A statement of ethical acceptability has been given to the research plan of the course by the University of Helsinki’s Research Ethics Committee in the Humanities and Social and Behavioral Sciences (statement 75/2024), and the research will be conducted according to the Finnish National Board on Research Integrity (TENK) guidelines
[47]. Informed consent from all the participants is obtained at the beginning of the course, which is signed online. The participants are informed about the study with a study information sheet in the course area. In addition, a data privacy notice is given to the participants in the course area detailing the research protocol, data collection and management, and participants’ rights following the General Data Protection Regulation of the European Union. Participants are informed about the possibility to withdraw from the research at any time, and the course can be completed without participation in the research.

For RQs 1 to 3, all data are collected in the secured course area and downloaded and backed up on secure servers with restricted and password-protected access. The data comprising the questionnaire data used in the study are pseudonymized before analysis. Participants are distinguished in the data by an identification number. The identifiers are not shared outside the research group. The contact information of the participants is stored separately from the research data. The qualitative interview data are recorded and transcribed. The transcriptions and the written assignments used in research will be anonymized as much as possible by removing locations and other identifying information from the transcripts; names are replaced with identification numbers. The data with identifiers will be destroyed 10 years after the end of the research project.

For RQ 4, all interview data will be collected via the University of Helsinki’s Zoom, where interview sessions are recorded. The data will be pseudonymized during transcription, and any potentially identifying details (such as names, colleagues, units, or departments) will be removed. The data is backed up on secure servers with restricted and password-protected access. Only the research team will have access to the recordings and transcripts. Audio recordings will be deleted after transcription. Neither the employer nor any other third party will have access to interview material, and no individual participant will be identifiable in any reports, publications, or presentations. We will emphasize to participants that their employer will not be informed of their participation or responses, and participation or nonparticipation will have no impact on their employment.

## Results

As of the first data freeze in November 2025, a total of 265 participants had enrolled in the course and given their consent to participate in the research, and 113 participants have completed the course (Table 1). Among participants who completed the course, the mean number of days between questionnaires at T1 and T2 was 123, and the median was 109 days. The first data cut is expected to be published in late 2026 or early 2027. Preliminary results suggest that participants’ burnout scores at T1 reflect 3 distinct profiles and that the profiles experiencing the highest burnout scores are also more likely to drop out. Similarly, participants completing the course alone were more likely to drop out than those in a peer group.

**Table 1. T1:** Characteristics of the study sample recruited in the first data cut (N=265).

Background characteristics	Participants, n (%)
Job description	
Teaching and research staff	35 (13.2)
Other expert and support staff	226 (85.2)
Missing or N/A^a^	4 (1.5)
Course completion method	
Self-guided or alone	99 (37.4)
With a peer group	145 (54.7)
Missing or N/A	21 (7.9)

a N/A: not available.

## Discussion

### Overview

The aim of this paper was to develop an ACT-based well-being and working life skills course for academic staff, as well as to present our study design. The course was developed based on research on how to support academics’ well-being and working life skills to answer the current well-being problems they are facing [3]. Thus, the course was based on the principles of ACT [15], further fostering the development of psychological flexibility and working life skills.

During this course, each subprocess of psychological flexibility is addressed across the modules. In addition, several working life skills–related themes are interwoven throughout the entire course. We have built the course with pedagogical tools to support participants’ learning and engagement, in particular guided reflection and collaborative peer group work.

### Principal Findings

We anticipate that participants’ baseline burnout levels will be heterogeneous and will reflect at least 2 distinct burnout profiles. We also hypothesize that academic staff will report improvements in their well-being at the end of the course and that dropout rates are significantly different between different burnout profiles and participation formats.

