**Conclusions:**

If the intervention proves successful, it may serve as an important tool for improving academics’ well-being, working life skills, and engagement by understanding how this intervention can help academic staff members with different initial burnout levels. In addition, it can help to understand and solve individual challenges related to well-being in the academic workplace.

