### Aims and Objectives

There is a need to enhance academics’ well-being, yet effective, research-based, and feasible tools are limited. Accordingly, this study pursues 4 goals. First, we aim to develop an online ACT-based intervention for academic staff that integrates working-life skills, specifically time management and reflective skills, and is feasible to complete within demanding work environments. Second, we aim to evaluate the intervention quantitatively by identifying latent burnout profiles among university staff and examining whether changes in burnout, psychological flexibility, perceived stress, overall well-being, and procrastination differ across profiles and participation formats. Third, we aim to examine participant engagement and retention by investigating whether dropout differs across latent burnout profiles and according to participation formats (individual vs group-based). Fourth, we aim to explore participants’ lived experiences of the intervention qualitatively, with a particular focus on psychological flexibility processes and on which of these processes’ participants perceive as most meaningful for their well-being and functioning at work.

Our research questions (RQs) are as follows:

RQ 1. What latent burnout profiles can be identified among staff at the University of Helsinki, and to what extent do the effects of the online ACT-based intervention differ between them?RQ 2. How do observed pre-post changes in burnout, psychological flexibility, perceived stress, and overall well-being vary across burnout profiles and participation formats?RQ 3. How do latent burnout profiles differ in training dropout rates, and does participation in group-based versus self-guided online ACT-based training relate to dropout?RQ 4. How do participants describe their experiences of psychological flexibility processes following participation in a digital ACT-based intervention, and which of these processes do they perceive as most meaningful in supporting their well-being and functioning in their work?

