#### Setting and Participants

This study is conducted at the University of Helsinki where the course is open to all university personnel, including teaching faculty, researchers, and administrative and support staff. The course has been available since fall 2023. For RQs 1 to 3, participants are recruited to attend the course via regular communications and advertisements to university personnel via university HR, intranet, email, and website. All willing participants can attend the course, and there are no exclusion criteria in the study. Participation in the research is optional, and participants can study in the course without consenting to research. At the beginning of the course, participants are asked to give or decline their permission to use their questionnaire data and written responses for research purposes.

For RQ 4, a purposive subsample (N≈30‐40) will be recruited from participants who have completed the course for semistructured interviews. Sampling will be stratified according to the latent burnout profiles identified in RQ 1 in order to include participants from each profile and permit systematic comparison of experiential patterns across profiles. Separate written consent is given for the interviews before the start of the interview.

For RQs 1 to 3, data collection started in 2023 when the course was opened to all staff members. For RQ 4, data collection is scheduled to take place in fall 2026.

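### The well-being hypothesis, objective and conclusions are stated for academic staff, but only 35 of 265 participants (13.2%) are teaching or research staff, and the document does not hold to one target population

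*Protocol article*

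**What the plan says.** The protocol article describes its population in two ways.

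**Academic staff or academics.** The first aim reads "First, we aim to develop an online ACT-based intervention for academic staff that integrates working-life skills". The abstract's objective describes the course as meant for, and offered to, academic staff. The abstract's conclusions say that, if successful, "it may serve as an important tool for improving academics’ well-being, working life skills, and engagement", and refer to "how this intervention can help academic staff members with different initial burnout levels". The improvement hypothesis under Principal Findings is "We also hypothesize that academic staff will report improvements in their well-being at the end of the course". The Introduction builds its case largely on pressures of academic work, such as student numbers, programme supervision and publication targets.

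**University staff.** Under Setting and Participants, "the course is open to all university personnel, including teaching faculty, researchers, and administrative and support staff", and there are no exclusion criteria. The second aim and RQ 1 speak of staff of the university without limiting them to academics. So do the course title and the evidence gap described in the Introduction and under Comparison to Prior Work.

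Table 1 (Results) separates "Teaching and research staff" (35) from "Other expert and support staff" (226), with 4 missing, out of 265. The Statistical Analyses section describes change at group level and comparisons by burnout profile and participation format. Job category is collected but is not named in these analyses. The limitations mention selection bias and restricted generalizability in general terms, but not the job mix.

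**The concern.** A hypothesis should be about the population that the analysis estimates. Here the hypothesis and conclusions name a group that makes up about one in eight participants, while the planned estimate averages over everyone. A significant pooled improvement would then be read as confirming a benefit in academics, although it could arise almost entirely in other staff. The Introduction itself separates evidence from non-academic workplaces from evidence on academic workers, so the authors treat the distinction as relevant. At stake is who the published result applies to. The validity of the study for university staff as a whole is not in question.

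**Working it through.** **Inputs.** Results and Table 1: N = 265 enrolled and consenting; 35 teaching and research; 226 other; 4 missing; 113 completers. Abstract: recruitment target 300. Not given, therefore assumed: two-sided alpha of 0.05, the size of the changes, a common SD of change in both job groups, and completion by job category.

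**1. Reproduce the stated share.** 35 + 226 + 4 = 265. 35/265 = 13.2%, as printed. The 95% Wilson interval is 9.7% to 17.8%. Among those with known job type, 35/261 = 13.4% and 226/261 = 86.6%. (226/265 is 85.3% where the table prints 85.2; this is immaterial.)

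**2. What the pooled change measures.** Pooled change = w × (change in teaching/research) + (1 − w) × (change in others), with w = 0.134.

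| Teaching/research | Others | Pooled | Power, paired t test, n = 113 |
|---|---|---|---|
| 0 | 0.5 SD | 0.866 × 0.5 = 0.43 SD | over 99% |
| 0 | 0.3 SD | 0.866 × 0.3 = 0.26 SD | about 78% |

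A significant pooled improvement is therefore compatible with no change in academics.

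**3. How many teaching and research staff complete.** The overall completion rate is 113/265 = 42.6%. Applied to the 35, this gives 35 × 0.426 = 14.9, about 15. The rate by job category is not reported, so a range is needed:

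| Assumed completion among the 35 | Completers | Share of 113 | Pooled change if 0 and 0.5 SD |
|---|---|---|---|
| 20% | 7 | 6% | 0.94 × 0.5 = 0.47 SD |
| 42.6% | 15 | 13% | 0.87 × 0.5 = 0.43 SD |
| 100% | 35 | 31% | 0.69 × 0.5 = 0.35 SD |

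Even in the most favourable row, other staff supply more than two thirds of the estimate.

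**4. Precision of a separate estimate.** The 95% half-width in SDs of change is t(0.975, n − 1)/√n.

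- n = 15: 2.145/3.873 = 0.55
- n = 35: 2.032/5.916 = 0.34
- n = 113: 1.981/10.630 = 0.19

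Power at n = 15 is 19%, 44% and 82% for paired standardized changes of 0.3, 0.5 and 0.8. The change detectable with 80% power is 0.78 SD at n = 15, against 0.27 SD at n = 113.

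**5. Does reaching 300 help?** With the same mix, 300 × 35/265 = 39.6 enrolled and 39.6 × 0.426 = 16.9 completing, with a half-width of about 0.51 SD. Even if all 35 people still to be recruited were teaching and research staff, they would be 70/300 = 23% of those enrolled.

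**The case against.** The strongest reply is that the article uses academic staff loosely for everyone employed at the university. The abstract says the course is offered to academic staff, while the Methods open the same course to all personnel, and the limitations call the course's participants busy academic staff. On that reading the hypothesis covers everyone enrolled and no inference is misdirected. The documents do not settle the matter. However, the term is never defined that way, the Introduction draws on academic pressures such as publication targets, and Table 1 splits the groups. On either reading the wording needs aligning.

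Other replies stand in part or in full:

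- Only the improvement hypothesis names academic staff. The profile expectation refers to participants, and the dropout hypothesis names no occupational group. It would be wrong to say that all the hypotheses have this problem.
- The conclusions are conditional on success, and the limitations already say that conclusions on effectiveness are limited. No claim about effect has yet been made.
- This is a condensed article, and covariate lists commonly sit in a fuller plan. The absence of job type from the short statistical section is therefore not a fault in itself.
- A reader might infer that job type confounds the comparisons by profile, format and dropout. Table 1 gives only marginal counts, and nothing in the article links job type to any of these. It is a possible confounder, not a demonstrated one.
- The figure of 15 completers rests on equal completion across job categories, which is not reported.

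**Conclusion.** The point holds as a mismatch between the stated target population and the population studied. The well-being hypothesis, the objective and the conclusions are worded for a group that is 13.2% of the first data cut, while the second aim and RQ 1 already refer to university staff. The group-level change will mainly describe other expert and support staff.

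The shares come straight from Table 1. The pooled changes of 0.43 SD and 0.26 SD illustrate what is possible under assumed effects; they do not predict the results. The precision figures assume the overall completion rate, but the conclusion does not depend on it, since teaching and research staff could be at most 31% of the current completers.

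A reader might go further and infer that the course does not help academics, or that the pooled result is uninformative. Neither is supported. No results by job category are given, the effect may be the same in both groups, and the pooled estimate remains relevant to university staff as enrolled.

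**What to change.** 1. Name university staff as the target population in the abstract's objective and conclusions and in the hypothesis under Principal Findings, matching the second aim and RQ 1.
2. Add the job mix (35 of 265 teaching and research staff) to Strengths and Limitations.
3. Report change by job category with confidence intervals, either descriptively or through a job-by-time term. A main effect of job type alone would not serve, because it leaves the time effect essentially pooled.
4. Draw no conclusion specific to academics from the pooled result.

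The cost is small: wording, and one breakdown by a variable already collected. The claim becomes less favourable, and the teaching and research estimate will be imprecise and should be presented as such.

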**Methods:**

We will conduct a single-arm, nonrandomized, and mixed methods study with baseline, postintervention, and 6-month follow-up assessments. We will use an explanatory sequential design in which qualitative data are used to explain and deepen the quantitative findings. The quantitative part of the study aims to recruit 300 participants from the University of Helsinki. Questionnaire data will be collected from the participants 3 times: at the beginning, at the end, and 6 months after the course for well-being–related measures such as burnout and working life skills such as time management and psychological flexibility. The participants will be clustered based on their initial burnout risk score using latent profile analysis. Differences in participants’ dropout, participation forms, and changes in well-being and working life skills during the course will be analyzed with mixed ANOVA. Qualitative data will be collected from reflective journals written at the end of the course, participants’ written goal statements, and interviews among willing participants. Reflective journals will be analyzed with qualitative content analysis, and interviews will be analyzed using thematic analysis.

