**Results:**

As of March 2026, a total of 265 participants had enrolled in the course and given their consent to participate in the research. The current data are being analyzed, and the results are expected to be published in late 2026 or early 2027.

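### The profile and dropout hypotheses are worded as anticipations, although matching preliminary results from 265 of the 300 planned participants are already reported; later analyses of the same people cannot confirm them independently.

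*Protocol article*

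**What the plan says.** The Abstract (Methods) sets the target: "The quantitative part of the study aims to recruit 300 participants from the University of Helsinki". The Results section gives the state of the data: "As of the first data freeze in November 2025, a total of 265 participants had enrolled in the course", of whom "113 participants have completed the course". It then reports, as preliminary, that "burnout scores at T1 reflect 3 distinct profiles and that the profiles experiencing the highest burnout scores are also more likely to drop out" and that "participants completing the course alone were more likely to drop out than those in a peer group". It adds that this first data cut is expected to be published in late 2026 or early 2027.

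The Discussion follows. Under Principal Findings the authors anticipate that baseline burnout "will reflect at least 2 distinct burnout profiles", and they hypothesise that well-being will improve and that "dropout rates are significantly different between different burnout profiles and participation formats".

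Aims and Objectives lists RQ1 and RQ3 as open questions without predictions, so in this article the hypotheses first appear after the results. Statistical Analyses plans chi-square tests and odds ratios for dropout by profile and by format. It does not separate participants already examined from those still to come. Strengths and Limitations does not mention the early look.

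**The concern.** Readers use a protocol article to tell which predictions came before the data. Here the profile prediction and both dropout predictions each have a matching result one section earlier, from most of the planned sample. A reader of the later paper could take a significant dropout difference as a prediction made in advance and then borne out, although the people who supply the test had largely supplied the preliminary finding.

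This bears on what RQ1 and RQ3 can conclude. Strengths and Limitations expects the dropout results to give practical guidance on how the course may be most beneficial, and for whom. The well-being hypothesis is not affected, because no early result is reported for it.

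**Working it through.** The article gives no alpha, power or sample-size calculation, so there is no figure of the plan to reproduce beyond the counts.

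**Inputs.** Target 300 (Abstract, Methods). First cut 265 (Results). Format known for 99 self-guided + 145 peer group = 244, with 21 missing (Table 1; 244 + 21 = 265). Two-sided alpha 0.05 is an assumption.

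**1. Hypotheses beside results**

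| Principal Findings | Results, first cut |
|---|---|
| At least 2 profiles | 3 profiles |
| Dropout differs by profile | Higher in the highest-burnout profiles |
| Dropout differs by format | Higher among those studying alone |
| Well-being improves | No early result reported |

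**2. Overlap**
- Enrolled: 265/300 = 88.3%, leaving 300 − 265 = 35.
- Known format: 244/300 = 81.3%. This takes format as known for everyone at 300. If format stayed missing at the same rate, 300 × 244/265 = 276 would have it, and 244/276 is again 88%.
- First-cut publication: Table 1 labels the 265 as the first data cut, so the overlap appears complete.

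**3. Error rate under no true difference.** Take the test statistics at n₁ and at 300 as bivariate normal with correlation √(n₁/300). This fits a two-group comparison, such as format, or the highest-burnout profiles against the rest.

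| | n₁ = 244 | n₁ = 265 |
|---|---|---|
| Correlation | 0.90 | 0.94 |
| P(significant at 300), hypothesis set before the look and tested once | 5% | 5% |
| P(significant at 300), given first look with \|z\| > 1 | 16% | 16% |
| P(significant at 300), given first look with \|z\| > 1.645 | 41% | 45% |
| P(significant at 300), given first look significant | 60% | 68% |
| P(either look significant) | 7.0% | 6.6% |

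The last row is 0.05 + 0.05 − P(both significant in the same direction). At 265, P(both) = 0.05 × 0.681 = 0.0341, which gives 0.0659.

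The article does not give the numbers behind each preliminary result, nor whether non-completers at the freeze had dropped out or were still in progress. If the first look rested on only 200 people, the 60 to 68% would fall to 46%.

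**4. Could new enrollees alone settle it?** Split 35 in the ratio 99:145, about 14 and 21. Under assumed dropout rates of 65% vs 50%, 70% vs 50% and 70% vs 45%, power is about 14%, 21% and 30%. Such a test would keep its 5% level but would say little.

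**Date of the look.** The Abstract gives the same count for a later date ("As of March 2026, a total of 265 participants had enrolled in the course and given their consent"). The two dates should be reconciled, since the date of the look matters here.

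**The case against.** A reader might infer that the hypotheses were formed from these data and that their tests therefore carry no error control. The article does not support that, for four reasons:

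- **Timing is not stated.** Publication after the look is not formation after the look. The Introduction gives a literature rationale for both dropout factors (baseline symptoms and guided versus self-guided format). The ethics statement on the research plan is numbered 75/2024, before the November 2025 freeze.
- **The wording is looser than the findings.** It says at least two profiles where three were seen, and gives no direction where a direction was seen. That is compatible with hypotheses set earlier.
- **The number of profiles is a model-selection result.** No 5% test is attached to it, so an error-rate argument does not apply to that half.
- **The article never calls these tests confirmatory.** It discloses the early results openly and labels them preliminary, without P values. The 60 to 68% needs a significant first look, which is not reported.

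All of this stands, and it removes the stronger reading. It does not remove the narrower one. The article does not let a reader tell which case applies, and even with hypotheses set earlier, a test correlated about 0.90 to 0.94 with one already seen is not independent evidence.

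**Conclusion.** The point holds as a matter of framing and interpretation. Three of the four predictions in Principal Findings had matching preliminary results from 88% of the planned sample (81% with known format), and the article does not date the predictions.

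The error rate depends on that date. It is 5% if the hypotheses were fixed before the look and are tested once, 6.6 to 7.0% if either look may count as success, and about 60 to 68% if a hypothesis was adopted because the first look was significant. These figures assume two-sided alpha 0.05, no true difference, and a first look at 244 to 265 people. Whichever case applies, the first-cut publication and the analysis at 300 cannot count as independent confirmation. The finding of at least two profiles is already met by the preliminary result and should not be presented as an open prediction.

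**What to change.** 1. In Principal Findings, and wherever RQ1 and RQ3 are reported, state that the profile and dropout results had been seen at the November 2025 freeze, and say when each hypothesis was set.
2. If a dated plan from before the freeze contains the hypotheses, cite it. If not, label the profile and dropout analyses exploratory, and report the planned odds ratios with confidence intervals instead of presenting them as tests of prior predictions.
3. Keep the language of hypothesis for the change in well-being, for which no early result is reported.
4. A separate display of later enrollees is optional and descriptive only, given about 14 to 30% power in 35 people under the assumed rates.

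The cost is wording. The RQ3 conclusion becomes exploratory unless an earlier dated plan is produced. No data collection or planned analysis has to change.
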